### **Data sources**

- The Danish National Patient Registry (inpatients since 1977, outpatient/emergency rooms since 1995)
- The Danish Cancer Registry (since 1943)
- The Civil Registration System (since 1968)
- The Danish National Health Service Registry (since 1990)
- The Danish National Prescription Registry (since 1995)
- Socioeconomic data (educational data since 1981, income and partnership data since 1980)

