## Analysis plan

### *Eczema exposed*

- Persons with a diagnosis of atopic eczema (ICD-8: 691; ICD-10: DL20) in the Danish National Patient Registry between 1 Jan 1977 and 10 February 2018.
- We include all primary and secondary diagnoses for eczema from admissions, hospital outpatient clinics and emergency rooms in the Danish National Patient Registry, including ongoing contacts (that is, persons who at the end of study period are in active follow-up in a hospital outpatient clinic).
- Index date = The earliest hospital record for atopic eczema (date of admission or first outpatient appointment).
- Only persons who are born in Denmark and living in Denmark on the index date (i.e. date of first record for eczema).

For the current study, we will further restrict the study population as follows:

- We will exclude eczema patients (together with their matched comparators) identified by an ICD-8 diagnosis recorded together with an additional (“modification”) code indicating that it potentially an uncertain/unverified/working diagnosis (c\_diagmod=1–7).
- We will exclude patients (together with their matched comparators) with inconsistencies in registration of status and residence in the Civil Registration System (recorded as alive but not living in Denmark but without an emigration date), as we assume that these patients are not living in Denmark and thus not eligible.
- To ensure that we have at least 1 year of registration history from included registries (except the prescription registry), we will only include patients (together with their matched comparators) with index date on 1 January 1982 or later. In the subanalysis on severity and in a sensitivity analysis, we restrict to those diagnosed on 1 January 1996 or later in order to ensure one year of registration history in all databases.
- To ensure at least 1 year of follow-up after start of eligible follow-up (available until 30 June 2017), we will include eczema patients until 30 June 2016.
- We will exclude eczema patients (together with their matched comparators) with a record for any cancer (except non-melanoma skin cancer) before or on index date (see Table 2). That is, we will not only exclude those with history of the cancer outcome of interest. However, in analyses of non-melanoma skin cancer specifically, we will exclude those with previous history of this cancer as well.

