### Sensitivity analyses

8. We will examine if the association is reduced by adjustment for time-varying systemic treatment for eczema. The study is likely insufficiently powered to examine for effect measure modification by immunosuppressive treatments.

**Table 8. Number of events, accumulated person-time, and HRs for cancer associated with eczema, Denmark. Adjusting additionally for systemic treatment for eczema.**

|                          | N | events | P-Y
at
risk | Rate
per
1,000 | Hazard ratio and 99%
confidence interval  |                    |
|--------------------------|---|--------|-------------------|----------------------|----------------------------------------------------------|--------------------|
|                          |   |        |                   |                      | Unadjusted                                               | Mediation
model |
| Any cancer               |   |        |                   |                      |                                                          |                    |
| Unexposed                |   |        |                   |                      |                                                          |                    |
| Exposed                  |   |        |                   |                      |                                                          |                    |
| Lung cancer              |   |        |                   |                      |                                                          |                    |
| Unexposed                |   |        |                   |                      |                                                          |                    |
| Exposed                  |   |        |                   |                      |                                                          |                    |
| Breast cancer            |   |        |                   |                      |                                                          |                    |
| Unexposed                |   |        |                   |                      |                                                          |                    |
| Exposed                  |   |        |                   |                      |                                                          |                    |

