 Unexposed  
 Exposed  
 Leukemia  
 Unexposed  
 Exposed  
 Meningioma  
 Unexposed  
 Exposed  
 Cancer of the brain, hypophysis,  
 corpus pineale and ductus  
 craniopharyngealis  
 Unexposed  
 Exposed  
 Spinal cord, cranial nerve and  
 other CNS tumours  
 Unexposed  
 Exposed

---

Estimated hazard ratios from Cox regression with time since index date as underlying timescale, stratified by matched set.

Unadjusted: No adjustment.

Mediation model: Adjusted additionally for time-varying lifestyle-related diseases.

10. We will repeat the main analysis additionally adjusting for immunosuppression (immunosuppressive disorders or drugs).

---

**Table 10. Number of events, accumulated person-time, and HRs for cancer associated with eczema, Denmark. Adjusting additionally for immunosuppression.**

---

|                 | N | events | P-Y
at
risk | Rate
per
1,000 | Hazard ratio and 99%
confidence interval  |                    |
|-----------------|---|--------|-------------------|----------------------|----------------------------------------------------------|--------------------|
|                 |   |        |                   |                      | ‘Unadjusted’                                             | Mediation
model |
| Any cancer      |   |        |                   |                      |                                                          |                    |
| Unexposed       |   |        |                   |                      |                                                          |                    |
| Exposed         |   |        |                   |                      |                                                          |                    |
| Lung cancer     |   |        |                   |                      |                                                          |                    |
| Unexposed       |   |        |                   |                      |                                                          |                    |
| Exposed         |   |        |                   |                      |                                                          |                    |
| Breast cancer   |   |        |                   |                      |                                                          |                    |

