Unadjusted: Adjusted additionally for **immunosuppression**.

Mediation model: Adjusted additionally for time-varying lifestyle-related diseases **and immunosuppression**.

11. We will repeat the main analysis additionally adjusting for use of **oral corticosteroids**. We will define use as a time-updated never/ever variable. Thus, individuals classified as exposed if they ever have a prescription for an oral corticosteroid, with status changing at the first prescription for an oral corticosteroid.

---

**Table 11. Number of events, accumulated person-time, and HRs for cancer associated with eczema, Denmark. Adjusting additionally for oral glucocorticoids.**

---

| N | events | P-Y
at
risk | Rate
per
1,000 | Hazard ratio and 99%
confidence interval  |                    |
|---|--------|-------------------|----------------------|----------------------------------------------------------|--------------------|
|   |        |                   |                      | ‘Unadjusted’                                             | Mediation
model |

---

---

|                                  |
|----------------------------------|
| Any cancer                       |
| Unexposed                        |
| Exposed                          |
| Lung cancer                      |
| Unexposed                        |
| Exposed                          |
| Breast cancer                    |
| Unexposed                        |
| Exposed                          |
| Prostate cancer                  |
| Unexposed                        |
| Exposed                          |
| Melanoma skin cancer             |
| Unexposed                        |
| Exposed                          |
| Keratinocyte skin cancer         |
| Unexposed                        |
| Exposed                          |
| Lymphoma                         |
| Unexposed                        |
| Exposed                          |
| Multiple myeloma                 |
| Unexposed                        |
| Exposed                          |
| Leukemia                         |
| Unexposed                        |
| Exposed                          |
| Meningioma                       |
| Unexposed                        |
| Exposed                          |
| Cancer of the brain, hypophysis, |
| corpus pineale and ductus        |
| craniopharyngealis               |
| Unexposed                        |
| Exposed                          |

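### Oral corticosteroid use cannot be observed before 1995, yet analysis 11 adjusts for it in a cohort from 1982; analyses 8 and 10 share part of the gap

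*Protocol*

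**What the plan says.** Under Data sources, the protocol lists "The Danish National Prescription Registry (since 1995") and "The Danish National Patient Registry (inpatients since 1977, outpatient/emergency rooms since 1995").

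Under Eczema exposed, it admits patients "with index date on 1 January 1982 or later". The stated aim is "at least 1 year of registration history from included registries (except the prescription registry"), so the main cohort is knowingly built without prescription look-back. The same section says that for severity and for one sensitivity analysis "we restrict to those diagnosed on 1 January 1996 or later in order to ensure one year of registration history in all databases". Item 6 under Subgroup analyses extends this restriction to activity, and item 13 is the sensitivity analysis meant.

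Three other sensitivity analyses add a treatment-related covariate:

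- Item 8: "We will examine if the association is reduced by adjustment for time-varying systemic treatment for eczema".
- Item 10: "We will repeat the main analysis additionally adjusting for immunosuppression (immunosuppressive disorders or drugs").
- Item 11, oral corticosteroids: "We will define use as a time-updated never/ever variable", changing at the first prescription.

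Items 10 and 11 are described as reruns of the main analysis, and item 8 names no index-date restriction. All three therefore use the cohort from 1982.

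**The concern.** The protocol recognises in three places that a variable built on prescriptions needs index dates from 1996, and omits the restriction in the three tables that adjust for drugs. A user before 1995 is coded as a non-user until a later prescription appears, and permanently if none does. Adjustment for a covariate recorded in this way removes only part of the effect it is meant to remove.

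The secondary aim names systemic immunosuppressive treatments. Item 8 concedes that the study is probably too small to examine effect modification by them, so these adjustments are most of what remains for that aim. A hazard ratio that stays raised because use was not recorded could be misread as evidence that treatment does not account for the association.

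**Working it through.** The protocol gives no sample size, event count or person-time, so there is no figure of its own to reproduce.

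**1. What feeds each covariate** (Table 3 under Covariables, and item 11)

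| Analysis | Sources | Before 1995 |
|---|---|---|
| 11, oral corticosteroids | Prescriptions only | Unobservable |
| 8, systemic treatment | Prescriptions and Patient Registry procedure codes | Incomplete; zero cannot be shown |
| 10, immunosuppression | ICD-8 and ICD-10 diagnoses, procedure codes, drug codes | Diagnoses from inpatient records since 1977; prescription part missing |

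The protocol does not say from when the procedure codes were in use, and outpatient records begin only in 1995.

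**2. Consequence in the model**

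Comparators take the index date of their matched patient. The Cox model is stratified on matched set, with time counted from that date. At any event, all members of the risk set are thus at the same calendar date. If that date is before 1995, the corticosteroid covariate is 0 for all of them. The set carries no information on the corticosteroid coefficient and gives a plain unadjusted eczema contrast, inside a table labelled as adjusted.

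**3. How much person-time is affected**

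Inputs: entry 1982.0 to 2016.5, follow-up to 2017.5, prescriptions from 1995.0. Assume uniform entry and no loss.

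- Total: (35.5² − 1²)/2 = 629.6 units.
- Before 1995: 13²/2 = 84.5 units; 84.5/629.6 = 13.4%.
- Persons indexed before 1996: (35.5² − 21.5²)/2 = 399 units; 399/629.6 = 63.4%. Of these, (399 − 84.5)/399 = 78.8% falls from 1995 onward, when prescriptions are visible.

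Other assumptions:

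- Accrual from 1995 five times the earlier rate, no loss: index before 1995 gives (35.5² − 22.5²)/2 = 377; later index gives 5 × (22.5² − 1²)/2 = 1,263.1; 84.5/1,640.1 = 5.2%.
- Entry falling 2% a year with 2% annual loss: 17.9%.

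The pre-1995 share is therefore roughly 5-18%.

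**4. Illustration of the bias (every rate assumed)**

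Simulated matched sets were analysed with the stratified Cox model. The inputs were corticosteroid start at 4% a year in eczema and 1.5% in comparators, ten years of history before index, a corticosteroid hazard ratio of 1.5 or 2.0, and a true eczema hazard ratio of 1.0.

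| Eczema hazard ratio | Earlier users never refill after 1995 | Earlier users refill (0.2 or 1.0 per year) |
|---|---|---|
| Unadjusted, from 1982 | 1.12-1.23 | 1.10-1.22 |
| Adjusted, full history | 0.99-1.01 | 0.98-1.01 |
| Adjusted, records from 1995, cohort from 1982 | 1.08-1.16 | 1.01-1.05 |
| Adjusted, records from 1995, index from 1996 | 1.03-1.09 | 0.98-0.99 |

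Truncated records leave part of the bias in place, more so when earlier users do not reappear. The 1996 restriction reduces it. It does not remove it entirely if use ended before 1995.

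**5. Does item 13 already cover this?**

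No. The Table 13 footnote adds only lifestyle-related diseases to the model.

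**The case against.** The strongest reply is that the gap is disclosed, touches only sensitivity analyses and is partial. The prescription registry is openly exempted from the look-back rule, and no primary estimate uses these covariates. On the assumptions above, at least 82% of person-years fall when prescriptions are observed, and status updates at the first one recorded. This stands as a limit on severity. It does not explain why the restriction is applied to severity, activity and item 13 but not here.

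A second reply is that analyses 8 and 10 have other sources. For analysis 10 this largely stands, because disorders are coded from hospital diagnoses. For analysis 8 it stands in part. However, severe eczema draws on similar procedure and prescription codes, plus admissions recorded since 1977, and the protocol still restricts severity to 1996.

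A reader might infer more than the documents support:

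- **That all three covariates must be zero before 1995.** This is true only of oral corticosteroids.
- **That the adjusted hazard ratio will hardly move.** In the illustration it moves from 1.10-1.23 to 1.01-1.16, and its true movement cannot be derived.
- **That the 63% of person-years from persons indexed before 1996 is unobserved.** Most of it falls after prescriptions begin. The figure also assumes equal accrual before and after 1995, which is doubtful because outpatient and emergency diagnoses enter only then.
- **That the pre-1995 share of cancers exceeds its share of person-years.** This is not shown. If cancer rates rise 3-9% per year of follow-up, with no loss and accrual from 1995 one to five times the earlier rate, that share is 3-10% of events, against 5-13% of person-years.

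**Conclusion.** The point holds in limited form. In analysis 11 the covariate is unobservable before 1995, and every risk set from those years gives an unadjusted contrast. In analyses 8 and 10 drug capture is incomplete before 1995, less seriously so for analysis 10.

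The affected person-time is about 13% with uniform entry and no loss, and roughly 5-18% across the assumptions tried. Past users who stopped before 1995 add misclassification after that date too.

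Under-adjustment is the expected direction if the drugs are commoner in eczema and raise cancer risk. The documents do not establish either condition in figures, so the size of the bias remains unknown. The primary estimates are unaffected. The protocol's own 1996 rule, applied elsewhere for the same reason, makes the omission worth correcting.

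**What to change.** Run analyses 8, 10 and 11 also in persons with index date on or after 1 January 1996, the population of item 13. Compare each adjusted hazard ratio with the Table 13 unadjusted and mediation hazard ratios, so that covariate and population do not change together. For analysis 11, name the restricted version as the one to interpret. For analyses 8 and 10, report both versions and footnote the incomplete drug capture before 1995.

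The restriction should be added beside the planned tables, because replacing them would discard validly recorded immunosuppressive disorders and many events. It drops 14.0 of 34.5 entry years (40.6%). With accrual from 1995 one to five times the earlier rate, cancer rates rising 3-9% per year of follow-up and no loss, it drops about 35-80% of events.

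The cost is plan wording and extra columns or tables on a population already planned. The restricted versions will have wider intervals, and some rare-cancer rows may fall below the protocol's 20-event rule for publication.

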## Analysis plan

Spinal cord, cranial nerve and  
other CNS tumours  
Unexposed  
Exposed

Estimated hazard ratios from Cox regression with time since index date as underlying timescale, stratified by matched set.

Unadjusted: No adjustment.

Mediation model: Adjusted additionally for time-varying lifestyle-related diseases.

13. We will repeat the main analysis among those with an index date on or after 1 January 1996 to ensure at least 1 year of prescription history for patients.

**Table 13. Number of events, accumulated person-time, and HRs for cancer associated with eczema, Denmark. Analysis restricting to index date on or after 1 January 1996.**

|                          | N | events | P-Y
at
risk | Rate
per
1,000 | Hazard ratio and 99%
confidence interval  |                    |
|--------------------------|---|--------|-------------------|----------------------|----------------------------------------------------------|--------------------|
|                          |   |        |                   |                      | Unadjusted                                               | Mediation
model |
| Any cancer               |   |        |                   |                      |                                                          |                    |
| Unexposed                |   |        |                   |                      |                                                          |                    |
| Exposed                  |   |        |                   |                      |                                                          |                    |
| Lung cancer              |   |        |                   |                      |                                                          |                    |
| Unexposed                |   |        |                   |                      |                                                          |                    |
| Exposed                  |   |        |                   |                      |                                                          |                    |
| Breast cancer            |   |        |                   |                      |                                                          |                    |
| Unexposed                |   |        |                   |                      |                                                          |                    |
| Exposed                  |   |        |                   |                      |                                                          |                    |
| Prostate cancer          |   |        |                   |                      |                                                          |                    |
| Unexposed                |   |        |                   |                      |                                                          |                    |
| Exposed                  |   |        |                   |                      |                                                          |                    |
| Melanoma skin cancer     |   |        |                   |                      |                                                          |                    |
| Unexposed                |   |        |                   |                      |                                                          |                    |
| Exposed                  |   |        |                   |                      |                                                          |                    |
| Keratinocyte skin cancer |   |        |                   |                      |                                                          |                    |
| Unexposed                |   |        |                   |                      |                                                          |                    |
| Exposed                  |   |        |                   |                      |                                                          |                    |
| Lymphoma                 |   |        |                   |                      |                                                          |                    |
| Unexposed                |   |        |                   |                      |                                                          |                    |
| Exposed                  |   |        |                   |                      |                                                          |                    |
| Multiple myeloma         |   |        |                   |                      |                                                          |                    |
| Unexposed                |   |        |                   |                      |                                                          |                    |
| Exposed                  |   |        |                   |                      |                                                          |                    |
| Leukemia                 |   |        |                   |                      |                                                          |                    |
| Unexposed                |   |        |                   |                      |                                                          |                    |
| Exposed                  |   |        |                   |                      |                                                          |                    |

